### Ethical approval

The study will be conducted in accordance with the ethical principles that have their origin in the Declaration of Helsinki. It has been reviewed and approved by the Office for Research Ethics Committees Northern Ireland (reference 07/NIR03/71) and has received approval from the Medicines and Healthcare products Regulatory Agency (reference 22761/0008/001-0001).

### The Intervention

Intervention A is a standard care body wash preparation (Johnsons Baby Softwash). Intervention B is a proprietary 5% tea tree oil (TTO)-enriched body wash preparation, since this formulation has proven efficacy in achieving MRSA decolonization [16]. Patients will be randomised to 5% TTO body wash (Novabac 5% Skin Wash) or Johnsons Baby Softwash. The Novabac 5% Skin Wash contains the active ingredient melaleuca alternifolia oil 50 mg/g. When participants are allocated to either intervention the nurse will have only the allocated preparation available for the entire duration of time in the ICU that they are enrolled in the study. A standardized washing protocol is followed for patient hygiene in the ICUs. However, the quantity of body wash to be applied to individual patients is likely to be variable, depending on several factors that cannot be easily controlled, such as body surface area. The quantity administered therefore will be allocated to the discretion of the nursing staff.

### Risks to patients from intervention

The risk to patients associated with each intervention is estimated to be low. This is based on data assimilated in a recent review of the toxicity of TTO which concludes that topical use of this agent is relatively safe and that adverse effects are minor, self-limiting and uncommon [22]. Furthermore, in a randomized controlled trial of 110 patients who received 5% topical TTO for five days in a study of MRSA decolonization, no participants experienced adverse effects and no premature discontinuation was necessary [16]. Cutaneous adverse effects appear to occur in a significant proportion of patients only if much higher concentrations of TTO are used [23]. Very low concentrations (<0.01%) of TTO are associated with the development of resistance to both TTO and antibiotics in MRSA in vitro. However, as we will use 5% which kills MRSA this does not facilitate the development of resistance. Nonetheless, we will collect data on resistance of MRSA to antibiotics throughout the study. Adverse effects will be monitored daily by incorporating a record of washing and adverse events in standard nursing records. If any adverse events occur they will be reported to the medical staff and treated appropriately. An adverse events form will be completed. The Belfast, and South Eastern HSCTs are sponsoring and providing indemnity for this study. Participant safety and well-being are protected by implementing standard operating procedures as set out in the Research Governance Framework and the Medicines for Human Use (Clinical Trials) Regulations, 2004.

### Data collection methods and assessments: TTO evaluation and PCR verification

Data will be collected in a standardized manner across both sites according to Standard Operating Procedures. In both sites, patients will have screening specimens for MRSA carriage (using conventional culture methods on nasal and groin samples) carried out as a component of routine care by the nurse responsible for their care on admission to the ICU. For pragmatic reasons, duplicate specimens for processing by the PCR assay will only be taken in the RICU in the Belfast HSCT. All specimens will be obtained prior to either intervention commencing and will consist of swabs from both the nose and groin of all patients. Patients whose admission screening is positive by either method will be removed from the study (see exclusion criteria).

To facilitate verification of the PCR assay in the Belfast HSCT study population, its results will be compared to the culture results. Where there is disagreement between the culture and PCR results both will be repeated. In instances when the culture is persistently positive but the PCR assay persistently negative, this will be recorded as a false-negative PCR result (assuming a true-positive culture result). In instances when the culture result is persistently negative but the PCR assay is persistently positive, this will be recorded as a true-positive PCR result (assuming a false-negative culture result). If either test is not consistently positive or negative, it will be recorded as equivocal.

The presence of established major risk-factors for MRSA will be recorded, so that each can be analyzed as a covariate. These are:

• Total number of antibiotic-days during the ICU episode [24-26].

• Age (blocked by 10-year intervals).

• Number of comorbidities

• Intravascular catheter-days (number of devices × number of days) [27,28].

• Length of ICU stay [28,29].

• Severity of illness on admission to ICU [29].

Several other MRSA risk factors exist, such as transfer from high prevalence clinical units, multiple prior hospitalizations and residence in a nursing home. However, if participants are culture-negative at the time of admission to ICU, then these factors are not significant and therefore will not be recorded.

End-of-study screening specimens will be obtained from all participants on ICU discharge or death to identify those patients in whom MRSA acquisition has occurred during the inpatient episode. Additional information regarding MRSA acquisition as a result of MRSA detection in other clinical specimens taken as part of routine care in the ICU will also be recorded. The time of swab collection will be recorded.

Quantity of body wash will be determined by counting the number of bottles used. Antibiotic consumption will be retrieved from prospectively generated computerized patient records. Compliance and adverse effects will be monitored daily by incorporating a record of washing (including time of washes) and adverse events in standard nursing records.

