## Methods

### Research hypotheses

The primary research hypothesis is that MRSA colonization among critically ill patients will be reduced by daily washing with 5% TTO body wash in comparison with a standard body wash (Johnsons Baby Softwash). The secondary hypotheses are that 5% TTO body wash is more cost-effective than a standard body wash (Johnsons Baby Softwash); and that there is no difference in sensitivity and specificity between a PCR-based assay for detection of colonization with MRSA and the standard culture method.

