#### Hypothesis 3: Verification of PCR assay

Agreement between MRSA screening results obtained by the PCR assay versus conventional culture with reference to the definitions of true and false positivity above will be evaluated, to estimate the sensitivity, specificity, positive and negative predictive values of the PCR assay in this population.

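### The PCR scoring rule never records a false positive, so specificity and PPV come out at 100% whatever the assay's reproducible error rate

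*Protocol article*

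**What the plan says.** The scoring rule is in the protocol article under Data collection methods and assessments: TTO evaluation and PCR verification. It has four parts.

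- Only discordant results are retested: "Where there is disagreement between the culture and PCR results both will be repeated".
- Culture persistently positive with PCR persistently negative: "this will be recorded as a false-negative PCR result (assuming a true-positive culture result)".
- The opposite persistent disagreement: "culture result is persistently negative but the PCR assay is persistently positive, this will be recorded as a true-positive PCR result", with culture assumed to be falsely negative.
- Anything else: "If either test is not consistently positive or negative, it will be recorded as equivocal".

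No third, independent test is named. The section Hypothesis 3: Verification of PCR assay then ties the analysis to this rule. Agreement "with reference to the definitions of true and false positivity above will be evaluated", and the purpose is "to estimate the sensitivity, specificity, positive and negative predictive values of the PCR assay in this population". Under Research hypotheses, the corresponding hypothesis is that "there is no difference in sensitivity and specificity between a PCR-based assay for detection of colonization with MRSA and the standard culture method".

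**The concern.** The assay under evaluation helps to define its own reference. When PCR is reproducibly positive and culture reproducibly negative, PCR is taken as right and culture as wrong. Repeating the same assay shows whether the result is reproducible, not whether it is true: a signal that arises repeatedly from something other than MRSA would pass this test every time.

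This sits badly with the Background, which sets out to verify the assay against culture, as the current standard, before it enters routine care. At stake are two of the four planned accuracy measures. If specificity and PPV are fixed by the scoring rule, they say nothing about reproducible errors, and a laboratory could adopt a non-specific test on the strength of them. The rule also takes every persistent positive culture as true, so culture's specificity is fixed at 100% too. The specificity half of the hypothesis then compares two constants.

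**Working it through.** **1. Enumerate the rule.** Each swab has a first culture, a first PCR, and (if retested) a repeat of each, giving 2^4 = 16 patterns.

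| First results | Patterns | Scored as |
|---|---|---|
| Both positive (not retested) | 4 | 4 true positive |
| Both negative (not retested) | 4 | 4 true negative |
| Culture+/PCR- | 4 | 1 false negative, 3 equivocal |
| Culture-/PCR+ | 4 | 1 true positive, 3 equivocal |

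Totals: true positive 5, true negative 4, false negative 1, equivocal 6, false positive 0.

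**2. Formulas.** Let a = both positive, b = persistent culture-/PCR+, c = persistent culture+/PCR-, d = both negative, with equivocals set aside.

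- Under the rule: specificity = d/(d+0) = 100%; PPV = (a+b)/(a+b+0) = 100%; sensitivity = (a+b)/(a+b+c).
- With culture as reference: specificity = d/(b+d); PPV = a/(a+b); sensitivity = a/(a+c).

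The rule's sensitivity exceeds a/(a+c) when b and c are both above zero, and equals it otherwise.

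**3. Illustration.** The article gives no PCR accuracy figures, so every input here is an assumption: 680 Belfast patients (1080 × 17/27, the trial sample size scaled by ICU beds), prevalence 5%, culture sensitivity 80% and specificity 100%, PCR sensitivity 90% and specificity 97%, the two tests' misses independent, discordances in carriers persistent, and half the PCR false positives reproducible.

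There are 680 × 0.05 = 34 carriers and 646 non-carriers. Expected counts:

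- Both positive: 34 × 0.8 × 0.9 = 24.48
- Culture+/PCR-: 34 × 0.8 × 0.1 = 2.72
- Culture-/PCR+ in carriers: 34 × 0.2 × 0.9 = 6.12
- Carriers missed by both: 34 × 0.2 × 0.1 = 0.68
- PCR false positives: 646 × 0.03 = 19.38, of which 9.69 reproducible and 9.69 equivocal
- PCR-negative non-carriers: 626.62

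| Measure | True | Under the rule | First-pass culture as reference |
|---|---|---|---|
| PPV, first pass | 30.60/49.98 = 61% | – | 24.48/49.98 = 49% |
| PPV, equivocals set aside | 30.60/40.29 = 76% | 40.29/40.29 = 100% | – |
| Specificity | 97% first pass; 626.62/636.31 = 98.5% with equivocals set aside | 627.30/627.30 = 100% | 627.30/652.80 = 96% |
| Sensitivity | 90% | 40.29/43.01 = 94% | 24.48/27.20 = 90% |

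**4. If equivocals counted against the assay.** PPV would be 40.29/49.98 = 81% against a true first-pass 61%. The 9.69 reproducible false positives would still sit in the numerator.

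**5. Range.** Take prevalence 5–10%, culture sensitivity 80–90%, culture specificity 100%, PCR specificity 90–99%, and all errors persistent. A true PCR sensitivity of 80% is then reported as 83–94%, and 90% as 92–97%. Over these settings (PCR sensitivity 80% or 90%), true PPV runs from 30% to 91% and is always reported as 100%.

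**The case against.** **Equivocals.** A reader might infer that specificity and PPV are 100% under every possible analysis. The article does not say how equivocals enter the denominators, and that detail may be left to the full protocol or analysis plan. If they were counted against the assay, both figures could fall below 100%. This stands as a qualification. It does not rescue the rule, because the reproducible culture-negative, PCR-positive result is scored explicitly and always in the assay's favour.

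**Sensitivity.** A reader might also infer that sensitivity is always inflated. It is not. Against culture there is no change if either persistent discordant cell is empty, and persistent false-positive cultures could offset or reverse the effect. The article assumes such cultures away.

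**Size.** Setting 61% against 100% compares a first-pass PPV with a figure obtained after repeat testing. Like for like the contrast is 76% against 100%.

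**Culture is imperfect too.** Taking culture as truth errs in the other direction. In the illustration 6.12 of the 25.50 culture-negative, PCR-positive results are real carriers, and PPV against culture is 49% when the truth is 61%. This stands, and it is why results against culture should be labelled as agreement.

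**Weight and recoverability.** PCR verification is one secondary objective, done at one site. The plan already lists agreement with culture as an outcome, and the individual results will exist to be re-scored. All true, but the article commits the accuracy estimates to the faulty definitions.

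**Conclusion.** The point holds. It concerns a rule the article states, not detail left to another document. A reproducible PCR-positive, culture-negative result can never count against the PCR, and no branch records a false positive. Specificity and PPV are therefore 100% whatever the reproducible error rate, subject only to the unstated treatment of equivocals, and the specificity half of the hypothesis cannot be refuted. This part is algebra and needs no assumed inputs.

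The effect on sensitivity is conditional: it needs both persistent discordant cells to be non-empty and positive cultures to be true. The percentages are illustrations on assumed inputs and do not predict this assay's performance. Nothing in the article shows that the assay is in fact non-specific.

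A reader might extend the criticism to the main trial result. The article does not support that: under Outcome measures, new colonization is defined by conventional culture, and the PCR scoring rule plays no part in its analysis.

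**What to change.** - In the main accuracy analysis, drop the rule that scores persistent culture-negative, PCR-positive results as true positives.
- Report first-pass PCR against first-pass culture in all Belfast patients swabbed, including those later removed for a positive screen. Present this as positive and negative percent agreement with exact confidence intervals.
- State that culture is an imperfect reference, so that specificity and PPV relative to culture are conservative.
- Present after-repeat results separately as descriptive, with equivocals shown. Give bounds with the persistent culture-negative, PCR-positive results scored first as all false positive and then as all true positive. In the illustration the PPV bounds would be 24.48/40.29 = 61% and 100%, which contain the like-for-like true value of 76%.
- Restate the PCR hypothesis as estimation with confidence intervals.

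The cost is a change of analysis wording; the swabs and test results are the same. The drawback is that apparent specificity and PPV become less favourable, because some carriers missed by culture will count against the PCR.

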## Background

Over the past ten years there has been a dramatic increase in the number of infections caused by MRSA in several countries, including the United Kingdom (UK) [1]; this pathogen is now endemic in hospitals throughout the country. It appears that although many patients begin by being colonized, without any clinically evident infection, between 30% and 60% of colonized critically ill patients subsequently develop an infection syndrome attributable to the organism [2,3]. In fact, colonization pressure (number of MRSA carrier patient-days/total patient-days) is a major independent predictor of MRSA infection in a given critically ill population [4].

MRSA infection appears to be associated with greater attributable mortality than infection with methicillin-sensitive Staphylococcus aureus (MSSA), based on a recent meta-analysis of bacteraemia outcomes [5], although this may reflect the vulnerability of the patient population infected by MRSA, rather than greater virulence of the organism *per se*. Nevertheless, compared to MSSA, infections with MRSA demand treatment with antimicrobial agents of greater toxicity and acquisition costs; many of these drugs also require frequent monitoring of serum levels, further adding to the total cost of therapy [1,5]. Moreover, MRSA infection is associated with prolonged length of hospital stay, including duration of Intensive Care Unit (ICU) stay; using data from the National Audit Office, nosocomial infection is estimated to be associated with, on average, 11 additional days in hospital and total costs of 2.8 times that of uninfected patients [6-10]. Indeed, even without progression to infection, colonized patients require increased healthcare resource in the numerous measures implemented to limit the spread of MRSA to other patients. Investigators in Canada, using a cost model, estimated the additional cost per patient episode arising from MRSA colonization (without infection) equivalent to £650 [11]. Applying these costs to local ICU surveillance data, new MRSA colonization alone may add around £65,000 per annum to cost of care in a 17-bed ICU, aside from costs of prolonged ICU stay.

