### Participants and sample size

All patients admitted to the ICUs during the study period will be eligible for inclusion in the study except those patients who fulfil the following exclusion criteria: less than 18 years of age; known to be colonized with MRSA at the time of admission; on admission, are judged as unlikely to remain in the ICU for at least 48 hours; are recruited, but whose pre-intervention MRSA screening tests are subsequently found to be positive (by standard culture); consent declined; and have a known sensitivity to TTO.

The primary outcome measure is the difference in MRSA colonization between groups at ICU discharge. The incidence of MRSA colonization during ICU admission in the study population is 13% (data obtained from the feasibility study conducted in one of the ICUs). A sample size of 1080 subjects (540 in each group) will have 80% power at a two-tailed significance level of 0.05 to detect a clinically significant difference of at least 40% in efficacy between 5% TTO and standard body wash. As the study will be confined to ICU, with nursing staff administering the study treatment, compliance will be guaranteed. Given the intensive monitoring in ICU, we do not expect any loss to follow-up.

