### Outcome measures

The primary outcome measure is new MRSA colonization during the inpatient episode in ICU, as defined by detection of MRSA by conventional culture methods in screening swabs of nose and groin, or in clinical specimens processed by the laboratory in the course of normal clinical care. This outcome measure is important as infection is typically preceded by colonization. The definition of colonization is clearly defined and unambiguous and it has established resource implications.

The secondary outcome measures are as follows: cost savings per case of MRSA colonization avoided; incidence of MRSA bacteraemia in each group; consumption of glycopeptide antibiotics, linezolid, rifampicin and fusidic acid; maximum increase in sequential organ failure assessment (SOFA) scores during inpatient episode, with reference to admission baseline; and agreement between MRSA screening results obtained by conventional culture and the PCR assay under evaluation.

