### Statistical analyses

#### Hypothesis 1: TTO evaluation

For continuously distributed outcomes, differences between groups will be tested using independent samples t-tests, analysis of variance (ANOVA) and analysis of covariance (ANCOVA) with transformations of variables to normality if appropriate, or non-parametric equivalents. Chi-square tests (or Fisher's Exact tests) will be used for categorical variables. Major risk-factors for MRSA will be analyzed as covariates. Efficacy of intervention will be analysed on an intention to treat basis. A P value of ≤ 0.05 will be considered significant. A single final analysis is planned at the end of the trial.

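### Three of the six covariates for the efficacy analysis accrue after randomisation, so an effect adjusted for them can be biased and may lose power

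*Protocol article*

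**What the plan says.** All references are to the protocol article.

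- **Recruitment of patients, randomisation and consent:** patients are randomised when they are admitted to the ICU.
- **Data collection methods and assessments:** "The presence of established major risk-factors for MRSA will be recorded, so that each can be analyzed as a covariate". The list has six items. Age, number of comorbidities and severity of illness on admission are fixed at baseline. The other three are "Total number of antibiotic-days during the ICU episode", intravascular catheter-days (devices multiplied by days) and length of ICU stay.
- **Statistical analyses, Hypothesis 1:** "Major risk-factors for MRSA will be analyzed as covariates". The sentence does not separate baseline factors from later ones. The same paragraph plans chi-square or Fisher tests for categorical variables and an intention-to-treat analysis of efficacy.
- **Outcome measures:** the primary outcome is new MRSA colonization during the ICU episode. Secondary outcomes include "consumption of glycopeptide antibiotics, linezolid, rifampicin and fusidic acid".
- **Cost-effectiveness evaluation:** additional ICU days and antibiotic consumption are among the resources to be costed as arising from colonization.
- **Background:** "MRSA infection is associated with prolonged length of hospital stay, including duration of Intensive Care Unit (ICU) stay".

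**The concern.** Covariate adjustment keeps the protection of randomisation only if the covariates cannot be influenced by treatment or outcome. Three of the listed variables do not meet that condition. They are totals over the whole ICU episode. Under the withdrawal rules, colonization ends the intervention but not participation, so the totals also count days after the event they are meant to help predict. The protocol uses the same kinds of quantity as results of MRSA in one section and as adjusters for MRSA in another.

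Two mechanisms are at stake. If colonization lengthens stay or adds antibiotic-days, the model conditions on a consequence of its own outcome. If TTO changes stay or prescribing, which is conceivable in an open-label trial, the model removes part of the treatment effect or creates an apparent one. Either way the adjusted estimate is not the total effect that an intention-to-treat analysis aims at.

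**Working it through.** **1. What the planned sample size rests on.** The plan states: "A sample size of 1080 subjects (540 in each group) will have 80% power at a two-tailed significance level of 0.05". The effect to be detected is 40%, and the control incidence is 13%. Reading 40% as a relative reduction, the TTO incidence is 0.13 × (1 − 0.40) = 0.078.

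Pooled-variance formula for two proportions, with mean proportion (0.13 + 0.078)/2 = 0.104:

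n per arm = [1.960 × √(2 × 0.104 × 0.896) + 0.8416 × √(0.13 × 0.87 + 0.078 × 0.922)]² / (0.13 − 0.078)²

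= [1.960 × 0.4317 + 0.8416 × 0.4301]² / 0.002704 = 1.4596 / 0.002704 = 539.8, rounded up to **540 per arm, 1080 in total**.

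This matches the plan, and power at 540 per arm is 80.0%. The sample size is therefore that of an unadjusted two-proportion comparison. The corresponding odds ratio (OR) is (0.078/0.922)/(0.13/0.87) = 0.57.

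**2. What adjustment could do.** The document gives no covariate strengths, so this part is illustrative. Assumptions:

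- one standard normal baseline severity factor U;
- log stay before any effect of colonization = log 6 + 0.4U + normal error (SD 0.6);
- logit of colonization rises by 0.8 per unit of log stay and 0.3 per unit of U, calibrated to 13% and 7.8% (or 13% in both arms);
- colonization multiplies stay by a factor F;
- 540 per arm and 1,500 simulated trials per row (600 for the last row).

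Each cell gives the OR and the proportion of trials rejecting at two-sided 0.05.

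| Scenario | Treatment only | + severity | + severity + stay |
|---|---|---|---|
| Effect, F = 1 | 0.564 / 0.807 | 0.552 / 0.812 | 0.544 / 0.820 |
| Effect, F = 1.35 | 0.561 / 0.799 | 0.549 / 0.814 | 0.533 / 0.796 |
| Effect, F = 2.0 | 0.564 / 0.800 | 0.551 / 0.813 | 0.518 / 0.746 |
| Effect, F = 2.7 | 0.562 / 0.803 | 0.550 / 0.813 | 0.503 / 0.651 |
| Effect, TTO shortens stay 20%, F = 1 | 0.565 / 0.816 | 0.552 / 0.822 | 0.649 / 0.525 |
| Effect, TTO shortens stay 20%, F = 2.0 | 0.562 / 0.813 | 0.550 / 0.826 | 0.971 / 0.049 |
| No effect, F = 1 | 0.998 / 0.065 | 0.998 / 0.060 | 0.999 / 0.071 |
| No effect, F = 2.0 | 1.000 / 0.054 | 1.000 / 0.049 | 1.001 / 0.055 |
| No total effect, TTO shortens stay 20%, F = 1 | 0.997 / 0.052 | 0.999 / 0.050 | 1.197 / 0.162 |

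Monte Carlo error near 0.80 is about √(0.8 × 0.2/1500) = 0.01.

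The loss of power comes from the standard error. At F = 2.7 the mean standard error of the log OR rises from 0.211 (severity only) to 0.294 (with stay). Then |log 0.503|/0.294 = 2.34 and Φ(2.34 − 1.96) ≈ 0.65. With severity only, |log 0.550|/0.211 = 2.83 and Φ(2.83 − 1.96) ≈ 0.81.

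**3. A second illustrative model** added all three totals and assumed 0, 5 or 11 mean extra days of stay and antibiotics after colonization. It gave ORs of 0.52, 0.49 and 0.46 with power of about 87%, 81% and 61%. The comparators were OR 0.57 with about 80% power unadjusted, and OR 0.56 with about 83% power adjusted for baseline severity.

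**4. Reading the two together.** With no feedback from colonization to stay and no effect of TTO on stay, adjustment costs nothing. With feedback, the OR moves away from 1 and power may fall. If TTO itself alters stay, the OR moves towards or past 1. The direction and size depend on quantities the document does not give.

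**The case against.** **Exposure time is a real risk factor.** A patient who stays longer has more chance of acquiring MRSA, so adjusting for stay looks natural. But the total mixes days at risk with days after colonization, and any shortening of stay by TTO would belong to its effect. Cutting exposure at the first positive specimen would help only partly: screening swabs are taken only on admission and at discharge or death, so a case found only at discharge would have nothing cut off.

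**The Background speaks of infection, not colonization.** This is correct. Its 11 extra days are hospital days for nosocomial infection. It gives 30% to 60% of colonized critically ill patients progressing to infection, so even if every extra day were an ICU day the average per colonized patient would be 0.30 × 11 = 3.3 to 0.60 × 11 = 6.6 days. That lies around the 5-day scenario (about 81% power), not the 11-day one (about 61%). However, the cost-effectiveness section ties additional ICU days to colonization itself, so feedback is plausible but unsized. Similarly, the four agent groups in the secondary outcome are only part of total antibiotic-days.

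**A valid unadjusted comparison is already planned.** This stands. The chi-square or Fisher test carries the sample size and is untouched. ANCOVA is named only for continuous outcomes, and no adjusted model for the binary outcome is written out. Which result is primary, and the form of the model, may properly be left to the analysis plan and are no part of this point.

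**Stronger readings.** A reader might infer that the adjusted effect is certainly biased and underpowered, or that the trial's primary comparison is invalid. The document supports neither. Some scenarios above show no loss or a gain. Part of the OR shift is non-collapsibility rather than bias: with no feedback the OR still moves from 0.56 to 0.54 in one model, and to 0.52 in the other. No passage supports a particular effect of TTO on stay or prescribing, so the scenarios with a 20% shortening show only what could happen.

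**Conclusion.** The point holds as a defect in a stated rule. The protocol names three post-randomisation totals as covariates for the efficacy hypothesis, and its own text treats extra ICU days and antibiotic use as results of colonization. An estimate adjusted for them is not the total intention-to-treat effect.

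The consequence is conditional. The adjusted effect can be biased either way and may lose power. Where colonization lengthens stay but TTO does not act on it directly, the illustrations run from no loss (82% and 87% with no feedback) to about 65% and 61% under strong feedback. If TTO also changed stay, the distortion could be larger, but nothing in the document allows that to be sized. All these figures rest on assumed covariate strengths.

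The damage is confined to the adjusted analysis. The unadjusted comparison, its 540 per arm and its 80% power stand.

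**What to change.** In the data collection section and under Hypothesis 1, restrict the covariates of the efficacy analysis to the baseline factors already listed: age, number of comorbidities, and severity on admission (the APACHE II score is scheduled at baseline in Table 1). Remove total antibiotic-days, intravascular catheter-days and length of ICU stay from that list. Report them by arm descriptively, or use them only in analyses labelled exploratory.

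The cost is analysis wording only. No new data are needed and the sample size stays at 1080. In the first simulation, power with baseline-only adjustment was 0.81–0.83 against 0.80–0.82 unadjusted, so nothing is lost under those assumptions. The unadjusted test need not be replaced to cure this defect.
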